## Monitoring

### Data monitoring

A formal data monitoring committee will not be convened for this research study. There will be quarterly reviews of any adverse reactions and serious adverse events/reactions reported and appropriate action taken.

### Monitoring

The monitoring plan for the study will document the intensity of monitoring required.

### Auditing

The trial may be audited by the sponsor (BSUHT) in accordance with their annual audit plan.

## Statistical analysis plan

Rint measurements will be summarised, by dosage arm and by polymorphism, using means, standard deviations, medians and interquartile ranges. To answer research question 1, post-bronchodilator Rint will be regressed on baseline Rint to increase the precision of the treatment effect estimate, and dosage regimens with 100 + 300 mg of salbutamol taken as the reference group. Adjusted differences in mean Rint will be reported together with 99 % confidence intervals and *p* values, with *p* < 0.01 chosen to be significant in light of the multiple testing. To answer research question 2, extending the above model, a binary variable indicating homozygosity or heterozygosity for arginine and the interaction terms between this variable and the dosage regimen indicator variables will be included in the model.

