### Measuring dose response to inhaled salbutamol using Rint

To span the entire plausible dose-response range in each individual child would be unethical, requiring an impractical long protocol and multiple Rint measurements, at an age when cooperation is notoriously difficult to achieve and maintain. We therefore plan to map out the dose-response curve using a sparse-sampling dosage schedule in which each individual child will receive just two successive doses, with Rint measurements at baseline and after the first and second dose. For the dose-response assessment using Rint, we used the same design as the one created by two of the investigators for a recent study (DORESI study NCT 01470755). There is an assumption that the measurements made after administration of the second dose reflect the sum of the first and second doses, i.e. that the two doses are additive, with no loss of potency for the first dose during the interval between the first and second measurements. The two doses to be administered in each individual child will be randomly determined from the options below and will be concealed from the researchers measuring the response using Rint. Children will be randomised to the four dosage schedules in the ratio 1:1:1:1.

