### Dosage schedules

The dosage schedules are as follows:100 μg salbutamol → +300 μg = 400 μg salbutamol100 μg salbutamol → +500 μg = 600 μg salbutamol200 μg salbutamol → +600 μg = 800 μg salbutamol200 μg salbutamol → +200 μg = 400 μg salbutamol

Thus these four dosage schedules will contribute the following data points to the dose-response curve covering the range 100–800 μg (Table 1).

**Table 1 Tab1:** Schedule of dose pairs to be tested

Dose studied	100 μg	200 μg	400 μg	600 μg	800 μg
1	√		√		
2	√			√	
3		√			√
4		√	√		

A schedule of assessments is given in Table 2.

**Table 2 Tab2:** Schedule of assessments

Schedule items	Enrolment	Randomisation	Baseline	Testing: Dose 1	Testing: Dose 2
Time point				T_0_	T_45 min_
Enrolment					
Eligibility screening	X				
Informed consent/assent	X				
Allocation		X			
Interventions					
Dose 1				X	
Dose 2					X
Assessments					
Clinical history	X				
Recent relevant medications	X				
Adverse events				X	X
Saliva sample (for DNA work)			X		
Rint assessment			X	X	X
Urine sampling				X	X

Rint measurement will be performed at baseline and 15 min after each of the two doses of salbutamol. The second dose of salbutamol will be given 30 min after the first dose. If the participant needs to take a bronchodilator within 12 h of the study visit, then the research appointment should be rescheduled. Rint measurements will be made as specified in the consensus guidelines [6]. Briefly, the child will be seated and breathing quietly through the apparatus, via a mouthpiece, with nose occluded by noseclip or fingers and with cheeks supported. If the child is unable to tolerate or use a mouthpiece, a facemask will be used for all three measurements. At each Rint measurement, a minimum of 10 flow interruptions will be carried out, with inspection of mouth pressure transients in real time, in order to achieve a minimum of five technically acceptable interruptions. The Rint measurement will be calculated as the median value of all acceptable interruptions.

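### The research question 1 model contrasts dosing schedules, so it never compares 100 or 200 μg with 400–800 μg and cannot deliver the planned dose-response curve

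*Protocol article*

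**What the plan says.** The section Measuring dose response to inhaled salbutamol using Rint sets the aim: "We therefore plan to map out the dose-response curve using a sparse-sampling dosage schedule". Each child has Rint measured at baseline and after each of two doses. The section assumes that "the measurements made after administration of the second dose reflect the sum of the first and second doses".

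The Dosage schedules section lists four schedules. The first is "100 μg salbutamol → +300 μg = 400 μg salbutamol"; the others are 100 then 600, 200 then 800, and 200 then 400 μg cumulative. It states that "these four dosage schedules will contribute the following data points to the dose-response curve covering the range 100–800 μg", and Table 1 shows five cumulative doses.

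The Sample size section (research question 1) plans to compare change from baseline between doses and refers to paired *t* tests. The Background asks whether a small dose such as 200 μg is adequate for most of these children.

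The Statistical analysis plan section gives the model for the first research question: "post-bronchodilator Rint will be regressed on baseline Rint to increase the precision of the treatment effect estimate". Exposure enters that model by schedule, and the same sentence fixes the comparator: "dosage regimens with 100 + 300 mg of salbutamol taken as the reference group". The research question 2 sentence confirms the coding: "the interaction terms between this variable and the dosage regimen indicator variables will be included in the model". No cumulative-dose term or within-child term is named. The reference group is given in mg where the schedules are in μg. I read it as the first schedule, but the units need reconciling.

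**The concern.** The design is organised by cumulative dose, with two dose levels per child and five in total. The model is organised by schedule. A schedule coefficient is a contrast between two randomised groups at the same step, so it can compare low first doses with each other, or high cumulative doses with each other, but not low with high. Low versus high is what research question 1 turns on: whether a small dose does as well as a larger one. As written, the trial could be analysed exactly to plan and still give no estimate of 200 v 400 or 200 v 800 μg. The model also gives two groups with the same cumulative dose separate treatment terms.

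**Working it through.** **1. The plan's own sample size figure.** Inputs from the Sample size section: difference 0.23, SD 0.19, significance 0.01 (two-sided assumed), power 90%, 24 per group.
- Two-sample, normal approximation: 2 × (2.576 + 1.282)² × (0.19/0.23)² = 20.3, so 21 per group.
- Two-sample *t* test: 22.03, so 23 per group.
- Paired *t* test: 13.6, so 14.

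The stated 24 is therefore close to a between-group figure, although the text speaks of paired tests.

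**2. Contrasts implied by the schedule model.** Each schedule against the reference (100 then 400 μg):

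| Schedule | Outcome after dose 1 | Outcome after dose 2 |
|---|---|---|
| 100 then 600 | 100 v 100 | 600 v 400 |
| 200 then 800 | 200 v 100 | 800 v 400 |
| 200 then 400 | 200 v 100 | 400 v 400 |

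Under additivity the 400 v 400 contrast has expectation zero, so it can check additivity but cannot show a dose effect. Changing the reference schedule does not help, because contrasts stay within a step. Stacking both readings under schedule indicators averages the two columns, which is not a dose contrast either.

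**3. Precision.** Inputs: 136/4 = 34 children per schedule; residual SD = 0.20 × √(1 − 0.6²) = 0.16, from the SD and baseline correlation in the research question 2 sample size. The correlation ρ between a child's two post-dose readings after baseline adjustment is not in the documents; I take 0.2 to 0.7.
- Schedule model, 600 v 400: 0.16 × √(1/34 + 1/34) = 0.039.
- Pooling the two 400 μg groups only: 0.16 × √(1/34 + 1/68) = 0.034.
- Repeated-measures model with five cumulative doses. Put a = 1/(1 − ρ²) and b = −ρ/(1 − ρ²). In units of 34/0.16², the information matrix has diagonal 2a, 2a, 2a, a, a (100, 200, 400, 600, 800 μg) and off-diagonal b for the pairs 100–400, 100–600, 200–800 and 200–400. Inverting it gives these standard errors:

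| Contrast | ρ = 0.2 | ρ = 0.5 | ρ = 0.7 |
|---|---|---|---|
| 600 v 400 | 0.033 | 0.030 | 0.025 |
| 200 v 400 | 0.026 | 0.022 | 0.018 |
| 200 v 800 | 0.031 | 0.026 | 0.020 |

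The schedule model estimates neither of the last two rows.

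**4. Identifiability.** 100 and 200 μg occur only after dose 1; 400, 600 and 800 μg only after dose 2. Adding a step (period) term to the five dose terms gives six columns of rank 5. Dose and time therefore cannot be separated for any cross-step contrast.

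**The case against.** Several points on the other side have force.

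*The Sample size section mentions paired tests, which within child would give 100 v 400, 100 v 600, 200 v 800 and 200 v 400.* A reader might infer that low and high doses are never compared anywhere in the plan; that goes too far. What stands is that the stated model does not compare them, the 24 per group does not match a paired calculation (14), and the Statistical analysis plan section contains no paired analysis. The two sections need reconciling.

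*Half the post-dose data are discarded.* A reader might infer that 136 of 272 readings go unused. The article does not say that only one reading is analysed; fitting the model at each step would use all 272. It would still not compare low with high doses.

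*The form of the curve may be in a fuller analysis plan.* This is fair, so the absence of a curve equation is not the point. The schedule coding and reference group, however, are positively stated.

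*The 400 v 400 contrast is useful.* It is, as a direct check of additivity. The fault lies in treating it as a dose comparison.

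*The planned contrasts are randomised; cross-step contrasts are not.* This is the strongest objection, and it stands. Additivity concerns drug effect. It does not cover learning, time or fading cooperation, which the article itself calls difficult to maintain at this age. The standard errors above do not reflect any such bias. The randomised contrasts should therefore be reported alongside the cumulative-dose model, not demoted to a sensitivity analysis.

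**Conclusion.** Wrong as written: the model stated for research question 1 cannot answer it. Whichever post-dose reading is meant, 100 and 200 μg are not compared with 400–800 μg, and this follows from the schedules alone without numerical assumptions.

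The gain in precision is secondary and depends on assumptions. For 600 v 400 the standard error falls from 0.039 to about 0.033–0.025, roughly 15–35% smaller, and pooling the 400 μg groups alone reaches 0.034. A reader might expect at least a 23% reduction from within-child correlations of 0.5–0.7. That holds only if those are correlations after baseline adjustment. If they are raw correlations, and each reading correlates 0.6 with baseline, they become (0.5 − 0.36)/0.64 = 0.22 to (0.7 − 0.36)/0.64 = 0.53, and the standard error is 0.033–0.029, about 15–25% smaller.

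The sample size is not the problem here.

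**What to change.** - State which post-dose Rint reading or readings form the outcome.
- Make the research question 1 model a baseline-adjusted repeated-measures model using both post-dose readings per child. Use cumulative dose (100, 200, 400, 600, 800 μg) as exposure, pool the two 400 μg groups, and include a within-child covariance.
- Use 100+300 v 200+200 only as a check of additivity.
- Report alongside it the randomised within-step contrasts: 100 v 200 after dose 1, and 400, 600 and 800 after dose 2.
- State that cross-step contrasts such as 200 v 400 and 200 v 800 are confounded with time, and rest on additivity and on no period or cooperation effect.
- Reconcile the paired-test wording in the Sample size section with this model, and the mg and μg units between sections.

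The cost is analysis wording and work; no further children or measurements are needed. The article reports 37 of the planned 156 children recruited by June 2016, so at that stage the change could be made well before recruitment was complete. The price is the added reliance on untestable period assumptions, which is why the randomised contrasts stay in the main report.

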## Sample size

### Justification for research question 1: defining the optimal dose of salbutamol

Can we define the dose of inhaled salbutamol that is appropriate for children aged 2 years 6 months old to 6 years 11 months old with recurrent wheeze?

We plan to compare the difference in change from baseline between different salbutamol doses. From the data by Beydon et al. [9], we would define the minimum clinically important difference (MCID) for paired *t* tests as mean −0.23, standard deviation (SD) 0.19, and set the threshold of significance at 0.01 to account for multiple *t* tests. In order to detect a worthwhile difference of this size between dosages with 90 % power, a minimum of 24 patients will be needed in each dosage group, giving a sample size of 96 patients.

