The ratio of children carrying Arg/Arg and Arg/Gly status to those with Gly/Gly is 60 %:40 %. A sample size of 133 (80 Arg and 53 Gly/Gly) would allow us to detect a difference of 0.08 unit between the groups (delta = 0.08, SD = 0.20; effect size = 0.4) with 80% power for 5% significance, assuming a correlation between baseline and post-bronchodilator measurements of 0.6. To allow randomisation of equal numbers to the four groups, the sample size should be increased to 136. In order to allow a sample size sufficiently large to answer both research questions, and to allow for up to 12 % of children being unable to perform the measurement (based on experience in our unit in this age range), we will recruit a sample size of 156 children. We intend to recruit these children over 36 months.

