## Assignment of interventions

Participants will be randomised to the various pairs of salbutamol doses by a member of the research team using a web-based system (http://www.sealedenvelope.com/). Those delegated the role of randomising participants will be assigned a sealed.envelope.com randomisation user name and password by the trial manager. To randomise a participant, the randomiser will follow the OpSal Randomisation Guide. The randomisation system will be accessed at the following website: https://www.sealedenvelope.com/bsuh/users.

At the point of consent, a participant identifier will be assigned to the patient using the Participant Number Assignment Log. To randomise a participant, the participant identifier and date of birth must be entered, and then the inclusion and exclusion criteria must be confirmed. The participant is then randomised to a dosage schedule. An email notification is then sent to the randomiser and the coordinating centre.

An allocation sequence has been generated with four possible dosage schedules on a 1:1:1:1 basis. There is no stratification. The randomisation code list was generated by the trial statistician, and it was uploaded onto the web-based system by the trial manager. The direct research team members do not have access to the randomisation code list; therefore, concealment of allocation sequence is maintained until the moment of assignment.

The researcher performing the Rint measurement on the participant will be blinded to the dosing schedule until after the assessment has been performed. Two members of the research team will be required for the study visit. Researcher 1 will perform the Rint measurements and will be blinded to the dosage schedule. This researcher must leave the room whilst the salbutamol is being administered to the participant and any associated paper work must be concealed from this researcher until the study assessments have been performed. Researcher 2 will be unblinded to the dosage schedule. Researcher 2 will randomise the participant using the web-based randomisation service (sealedenvelope.com) on the day of the visit and will then administer the salbutamol. Once the final Rint measurement has been performed, the dosage schedule can be revealed to members of the research team if necessary.

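### Age is available for every randomised child but is not in the Rint model; prespecifying it as a second covariate may add a little precision, mainly for question 2.

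*Protocol article*

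**What the plan says.** The Statistical analysis plan section of the Protocol article fixes the model for question 1: "post-bronchodilator Rint will be regressed on baseline Rint to increase the precision of the treatment effect estimate", with the 100 + 300 regimen as reference. Question 2 is answered by "extending the above model, a binary variable indicating homozygosity or heterozygosity for arginine and the interaction terms" with regimen. Age appears in neither model.

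Age is nevertheless known for each child. Under Assignment of interventions, "the participant identifier and date of birth must be entered" before a child can be randomised. The same section states of the allocation: "There is no stratification". Eligibility criteria admit children from 2 years 6 months to 6 years 11 months.

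The sample size for question 2 already takes credit for baseline adjustment: it uses "delta = 0.08, SD = 0.20; effect size = 0.4", "assuming a correlation between baseline and post-bronchodilator measurements of 0.6".

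**The concern.** The plan justifies its one covariate by precision. The same reasoning applies to any other baseline variable that predicts post-dose Rint and is already held without missing values. Age is an obvious candidate: the eligible range is wide for children this young, and no new measurement is needed.

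Question 2 has the most to gain. It drives the recruitment target, and its calculation gives 80% power with almost nothing to spare. If age predicts post-dose Rint beyond what baseline Rint already carries, leaving it out makes the intervals somewhat wider than they need be. Because allocation is simple and unstratified, mean age may also differ between arms by chance. A covariate fixed in advance settles how that is handled before anyone sees the data.

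**Working it through.** **Inputs from the documents.** Question 2: difference 0.08, SD 0.20, correlation 0.6, 80% power, 5% significance (taken as two-sided), 80 Arg carriers and 53 Gly/Gly. Question 1: "mean −0.23, standard deviation (SD) 0.19, and set the threshold of significance at 0.01 to account for multiple" tests; "with 90 % power, a minimum of 24 patients will be needed in each dosage group, giving a sample size of 96 patients". Recruitment is 156 with up to 12% unable to perform the measurement, so 156 × 0.88 = 137 evaluable, about 34 per arm.

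**Input not in the documents.** The share of the variance left after baseline Rint that age explains (its partial R², written R below). It is assumed, and shown as 0, 0.025, 0.05 and 0.10.

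**Step 1: reproduce the plan's figure for question 2.**
- Without baseline adjustment, the Gly/Gly group needs (1 + 53/80) × [0.20 × (1.960 + 0.842) / 0.08]² = 81.6 children, or about 205 in total.
- Baseline adjustment multiplies this by 1 − 0.6² = 0.64: 81.6 × 0.64 = 52.2, rounded up to 53. With 80 Arg carriers the total is 133, as stated.
- The residual SD after baseline is 0.20 × √0.64 = 0.16. The noncentral t distribution with 80 v 53 then gives 80.0% power. About 137 evaluable children are expected, only four more than 133.

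**Step 2: add age.** The residual SD becomes 0.16 × √(1 − R), and interval width is multiplied by √(1 − R). Power is for the overall genotype effect, not for the interaction terms.

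| Assumed R | Residual SD | Intervals narrower by | Power, 80 v 53 |
|---|---|---|---|
| 0 | 0.160 | 0% | 80.0% |
| 0.025 | 0.158 | 1.3% | 81.0% |
| 0.05 | 0.156 | 2.5% | 82.0% |
| 0.10 | 0.152 | 5.1% | 84.0% |

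The lost degree of freedom does not change these figures at one decimal place.

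**Step 3: what correlations would give such values of R?** Suppose age has the same correlation r with Rint before and after the dose, and the two Rint values correlate at 0.6. Then R = (r − 0.6r)² / [0.64 × (1 − r²)] = 0.25r² / (1 − r²).
- |r| = 0.3 gives 0.025.
- |r| = 0.4 gives 0.048.
- |r| = 0.5 gives 0.083.
- |r| = 0.6 gives 0.141.

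The last case would make age as good a predictor of post-dose Rint as the child's own baseline value. If instead age acts only through baseline Rint (correlation with post-dose Rint equal to 0.6r), R is exactly 0.

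**Step 4: question 1.** Read as a two-sample t test at two-sided 1%, the stated inputs need 23 per group against the stated 24. Power is 92.8% at 24 per group and 98.9% at 34. With R = 0.10 these become 95.4% and 99.5%. Power for this question is ample on the stated inputs with or without age.

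**The case against.** The strongest case against is that nothing here is wrong. Regression on baseline Rint is sound, it matches the sample size calculation, and age is not a stratification factor that the model must carry. The article does not exclude further covariates, and a separate analysis plan that is not shown may name some. This largely stands, and it is why the point is optional. It does not remove the point: the article does write down a model and gives precision as its reason, and the suggested addition is specific and nearly free.

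Three stronger readings are tempting, and the documents support none of them.
- A reader might infer that precision is certainly lost because the age range is wide. No passage relates age to Rint or to bronchodilator response, so the gain may be nil.
- A reader might infer that, because a correlation of 0.6 leaves 64% of the variance unexplained, age has much of it to explain. That remainder also holds measurement noise, individual response, dose and genotype effects. Only the association of age given baseline counts.
- A reader might infer that chance age imbalance under unstratified allocation biases the dose comparison. It does not: randomisation protects the comparison, the intervals already allow for chance imbalance, and any part that shows in baseline Rint is already adjusted for.

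**Conclusion.** The point holds as an optional improvement, not as an error. The stated model uses one covariate for the sake of precision, while a second candidate is held for every randomised child. Some precision may be given up, mainly for question 2. The size rests wholly on the assumed partial R² for age: from nothing to intervals about 5% narrower, and from about 80% to about 84% power for the overall genotype effect. The middle of that range, 1% to 3% narrower, corresponds to moderate correlations of about 0.3 to 0.4. No gain is claimed for the genotype-by-regimen interaction terms, for which no power was worked out. Question 1 has little to gain in power, and its randomised comparison is unbiased either way.

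**What to change.** Prespecify age in months at the study visit, derived from date of birth, as an additional linear covariate beside baseline Rint in the regression models for both questions. The cost is one line in the analysis plan and one degree of freedom out of about 130, with no extra data collection and no change to the sample size. The article reports the trial as open with 37 children recruited in June 2016, so at that stage the covariate could be fixed well before analysis. If the separate analysis plan already names age, nothing need change.

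### Research question 2 is sized as one pooled genotype comparison, but its stated model includes genotype-by-schedule interactions and does not name that comparison

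*Protocol article*

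**What the plan says.** The sample-size section for research question 2 puts forward one overall hypothesis: children carrying at least one Arg copy have a smaller peak response than Gly/Gly children. It is not tied to any dosage schedule. The calculation matches it: "A sample size of 133 (80 Arg and 53 Gly/Gly) would allow us to detect a difference of 0.08 unit between the groups". Its inputs are a standard deviation of 0.20 (so a standardised effect of 0.4), a power of 80%, a 5% level and a baseline-to-post correlation of 0.6. The genotype split is taken as 60:40. The total then becomes 136 so that the four schedules are equal, and 156 to allow for children who cannot do the measurement.

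The Statistical analysis plan section first describes the model for research question 1: post-bronchodilator Rint regressed on baseline Rint and the dosage regimens, with the 100+300 schedule as reference, 99% confidence intervals and p < 0.01. For research question 2 it extends this model with a binary Arg indicator, and "the interaction terms between this variable and the dosage regimen indicator variables will be included in the model". It does not say which coefficient, contrast or joint test answers the question, and it gives no significance level for it.

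**The concern.** When a model contains an indicator and its interactions with a reference-coded factor, the coefficient of the indicator is its effect in the reference category, not its overall effect. Here the Arg coefficient is the genotype difference among children on the 100+300 schedule, and the three interaction coefficients are departures from that difference in the other schedules. The pooled contrast behind the 133 is a combination of these four terms and is not printed as any one of them.

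This matters because research question 2 sets the size of the trial: research question 1 needs 96 children, and research question 2 raises that to 133 and then 136. If the genotype coefficient is read off the output, an effect of exactly the assumed size would probably be missed and could be reported as no Arg effect. If the test stays unnamed, the choice among several tests of very different power could be made after the data are seen.

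**Working it through.** **Inputs from the sample-size section for research question 2:** difference 0.08 kPa/L/s; SD 0.20; baseline/post correlation 0.6; 80% power; 5% significance (sidedness is not stated; two-sided reproduces the total); genotype ratio 1.5; 136 evaluable children, so 34 per schedule. **Assumptions:** the 0.08 difference holds in every schedule, and each schedule has the 60:40 mix, giving 20.4 Arg carriers and 13.6 Gly/Gly.

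**1. Reproduce the stated figure.** Adjustment for baseline gives a residual SD of 0.20 × √(1 − 0.6²) = 0.16.

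Gly/Gly group: (1.96 + 0.842)² × (0.16/0.08)² × (1 + 1/1.5) = 7.85 × 4 × 1.667 = 52.3, rounded up to 53. Arg group: 1.5 × 53 = 79.5, rounded up to 80. Total 133, as stated. An unadjusted SD of 0.20 would give 205 and a change-score SD of 0.179 would give 165, so the basis is a pooled, baseline-adjusted two-group comparison.

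Its SE is 0.16 × √(1/80 + 1/53) = 0.028, and its power is about 80%.

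**2. Genotype coefficient in the interaction model.** It uses the contrast within the 100+300 schedule.

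- SE = 0.16 × √(1/20.4 + 1/13.6) = 0.056.
- 0.08/0.056 = 1.43. Power at two-sided 5% is Φ(1.43 − 1.96) ≈ 29.7%, or 29.4% with a noncentral t on 136 − 9 = 127 df.
- With 133 children the t-based figure is 28.9%. Simulating the full model with a random genotype mix gave 27% to 28%.

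**3. Joint test of all four genotype terms.** Noncentrality = 4 × 1.428² = 8.16. An F test on 4 and 127 df has 59.6% power at 5%.

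**4. Genotype effect averaged over the four schedules, same model.** SE = 0.056/√4 = 0.028; 0.08/0.028 = 2.86; power 80.9% (t) to 81.5% (normal) with 136 children. Simulation with a random genotype mix gave 79% to 80%.

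**5. Genotype main effect, no interactions.** Simulated power was about 79% with 133 children and 80% with 136.

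| Test of research question 2 (136 children, 5%) | SE | Power |
|---|---|---|
| Genotype coefficient, 100+300 as reference | 0.056 | 29% |
| Joint 4-df test of genotype terms | – | 60% |
| Average over four schedules | 0.028 | 81% |
| Main effect, no interactions (simulated) | – | 80% |

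**6. If p < 0.01 were carried over.** The pooled or averaged effect would have 58.4% power (133 children) to 59.6% (136), by noncentral t.

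**The case against.** The strongest reply is that the article never commits to the reference-arm coefficient. It lists model terms and stops. The pooled contrast can be estimated from that same model with about 81% power, so including the interactions costs essentially nothing if the average is what is reported. Naming a contrast is often left to a separate analysis plan, which may exist. The interactions also have a purpose, because research question 2 asks about the dose suited to an individual child.

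Much of this stands. A reader might infer that the genotype hypothesis will be tested on a quarter of the data, or that the true power is 29% and the 80% is wrong. The documents support neither: the 80% belongs to the pooled comparison and reproduces, and no sentence makes the reference-arm coefficient the test. A reader might also infer that research question 2 will be judged at 1%. The p < 0.01 rule sits with research question 1 and is justified by its multiple tests, while research question 2 was sized at 5%; the 58% to 60% figure is therefore conditional. Low power for a single interaction term (about 17%) needs a scenario with the full 0.08 in one schedule and none in another, which the article does not pose, so nothing here rests on it.

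What the reply does not remove is the mismatch. The article does more than leave a detail open: it fixes the reference group and the interaction terms, and those terms do not produce the comparison it sized.

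**Conclusion.** The point holds as a mismatch between the stated model and the stated sizing basis, not as an error in the sample size. Under the article's own inputs, the tests that come directly from the model fall short of the planned 80%: about 29% for the genotype coefficient and about 60% for the joint test. A main-effect model, or a schedule-averaged contrast that the text does not mention, restores about 80%. These figures assume a constant difference of 0.08, residual SD 0.16, 34 evaluable children per schedule, a 60:40 genotype mix and two-sided 5%.

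**What to change.** Name the test for research question 2 before the data are analysed. Either of these delivers the power the trial was sized for:

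- the genotype main effect from a model with baseline Rint and schedule indicators, without interactions; or
- the genotype effect averaged over the four schedules, taken from the interaction model.

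State that it is tested at the two-sided 5% level used for sizing, and that the p < 0.01 criterion applies to research question 1 only. Report the genotype-by-schedule interaction as a separate, secondary joint 3-df test. The cost is a few sentences of analysis wording; recruitment, randomisation and data collection do not change.
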